### Statistical analysis

2.10.

To compare baseline characteristics between groups, we will use an independent-samples t-test for continuous variables and a *χ*^2^ Test for categorical variables. To analyze differences in primary outcomes, we will use repeated-measures analysis of variance. All statistical analyses will be conducted using SPSS (version 27.0; IBM) and R (version 4.0.5).

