### Outcomes

2.5.

The timeline for this study will be one week. Prehabilitation will be implemented one week before the surgery, and the follow-up period will comprise of the perioperative period until the patient's discharge from the hospital. The outcomes will be assessed at four different time points: before the intervention (T0), upon admission to the hospital (T1), before surgery (T2), and after surgery (T3, before hospital discharge). Table 1 shows the complete assessment timeline.

**Table 1 T1:** Overview of assessment.

Measurement	T0: baseline	T1: hospital admission	T2: 1 day before surgery	T3: after surgery (before hospital discharge)
6-minute walk distance (6MWD)	×	×	×	×
Preoperative anxiety (APAIS)	×	×	×	
Frailty (FFPC)	×		×	×
Nutrition risks (NRS2002)	×	×		
Prehabilitation experience (FSS)		×	×	
ICU delirium (CAM-ICU-7)				×
Postoperative delirium (4AT)				×
Health-related quality of life (EQ-5D-5l)	×	×	×	×
Length of ICU stay, days				×
Length of hospital stay, days				×
Length of mechanical ventilation, hours				×

**The primary outcome** was the change in functional capacity over time, measured as the difference in absolute change in 6-minute walk distance (6 MWD) between T0 and T2 (primary analysis), as well as between T0 and T3. In this regard, a change of 20 meters from the baseline was deemed significant, indicating either an improvement or deterioration. To conduct this evaluation, participants will be instructed to wear comfortable footwear and walk back and forth in a 20-meter stretch of hallway for 6 min, aiming to reach a point of exhaustion by the end of the exercise. The tests will be conducted under the supervision of a blinded assessor following a standardized procedure to minimize potential sources of error due to bias or different levels of encouragement.

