### Data collection and management

2.8.

At the baseline interview after randomization, demographic and clinical characteristics will be collected, including age, sex, BMI, ASA physical status class, comorbidities such as diabetes, hypertension, and hyperlipidemia, and Charlson Comorbidity index. Laboratory test results and assessment outcomes will be obtained from patients' electronic medical records, including serum hemoglobin, NRS 2002, HYHA, main diagnosis, and EuroScore. Additionally, data on daily exercise amount and intensity, diet details, and duration of mindfulness will be collected using a bracelet (Xiaomi Wristband 7, Xiaomi Technology Co., Ltd.). The 6 MWD test will be performed and recorded by trained researchers at our institution after providing standardized instructions and demonstrations of the tests. Patient-reported questionnaires will be administered, and the outcomes will be recorded by trained researchers. During the prehabilitation period, message interviews will be sent to patients every day, and feedback on their daily prehabilitation performance will be documented. After the surgery, information on the surgery, duration of ICU stay, and postoperative recovery will be obtained from electronic records. Patient identity and personal information will remain confidential unless consent is provided. All collected data will initially be recorded in a paper-based case report form and then entered into a digital database by an independent investigator.

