### Sample size

2.9.

We determined that a difference of 20 meters in the change in 6-minute walk distance (6 MWD) between T0 and the T2 (primary analysis) in the prehabilitation group compared to the control group was a meaningful clinical outcome based on a previous study (22). Consequently, we conducted a sample size calculation using G*Power (version 3.1.) for the repeated-measures ANOVA with an alpha error of 5% and power of 0.95, with two groups and four measurements. The estimated sample size required was 132 patients. To account for a 15% attrition rate during the intervention period, the target sample size was increased to 152 participants (76 per group).

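### The primary 6MWD effect is a raw T0–T2 change difference; using T0 as a covariate would be more precise at no cost in patients, and the planned baseline tests cannot do that job

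*Protocol article*

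**What the plan says.** Three statements in the protocol article fix the primary analysis.

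- **Effect measure.** Section 2.5 (Outcomes) has it "measured as the difference in absolute change in 6-minute walk distance (6 MWD) between T0 and T2 (primary analysis"), with T0 to T3 alongside. Section 2.9 (Sample size) sets the target on the same quantity: "a difference of 20 meters in the change in 6-minute walk distance (6 MWD) between T0 and the T2 (primary analysis").
- **Method.** Section 2.10 (Statistical analysis): "To analyze differences in primary outcomes, we will use repeated-measures analysis of variance". Section 2.9 sizes a "repeated-measures ANOVA with an alpha error of 5% and power of 0.95, with two groups and four measurements", and Table 1 lists 6MWD at T0, T1, T2 and T3. T0 is therefore one of the four repeated outcomes. No covariate is named.
- **Baseline data.** Section 2.10: "To compare baseline characteristics between groups, we will use an independent-samples t-test for continuous variables", with a chi-square test for categorical variables. No consequence is attached to the results.

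On timing, section 2.8 (Data collection and management) places the baseline interview after randomisation. It does not say when, relative to allocation, the T0 walk takes place.

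**The concern.** Subtracting T0 from T2 assumes that a patient who starts 10 m higher will finish 10 m higher. When the T0–T2 correlation is below 1 and the SDs are similar, that over-corrects: patients who start low tend to gain more by regression to the mean, and this adds noise to the arm comparison. A model that estimates the slope on T0 removes that noise and targets the same treatment effect.

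The planned baseline tests do not help. After randomisation any baseline difference is due to chance, so a significance test asks a question whose answer is already known, and its result changes nothing in the estimate.

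At stake is the width of the confidence interval around a 20 m target, from a measurement the trial already takes.

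**Working it through.** **Inputs from the document:** target 20 m in T0–T2 change; alpha 5%; power 0.95; two groups, four measurements; 132 evaluable, 152 enrolled (all section 2.9); allocation 1:1 (section 2.1).

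**Not in the document:** the SD of 6MWD or of its change, the standardised effect f, and rho. All values of these below are assumptions.

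**1. The plan's own figure.** Without f and rho, 132 cannot be derived from the stated inputs. Two assumed sets reach it:

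- Between-groups term, f = 0.25, rho = 0.5: lambda = f²·N·m/(1 + (m − 1)·rho) = 0.0625 × 132 × 4/2.5 = 13.2 on 1 and 130 df; power 0.9501.
- Group-by-time term, f = 0.10, rho = 0.7: lambda = f²·N·m/(1 − rho) = 0.01 × 132 × 4/0.3 = 17.6 on 3 and 390 df; power 0.953.

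The match is not unique, so the correlation behind 132 cannot be recovered. The target of 152 is 132 × 1.15 = 151.8, rounded up.

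**2. Variance of the two estimators.** With common SD s at T0 and T2, per-patient variance is:

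- raw change: 2s²(1 − rho)
- T2 adjusted for T0: s²(1 − rho²)

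The ratio is (1 + rho)/2, so the information lost is (1 − rho)/2. If the SDs differ (s0 at T0, s2 at T2), the change-score variance exceeds the adjusted variance by (s0 − rho·s2)², which is never negative.

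**3. Size over a range of rho.** Take the plan's 95% power at 132 at face value for a 20 m difference in change. With 66 per arm the implied SD of change is 20/[(1.960 + 1.645) × √(2/66)] = 31.9 m. Then (normal approximation):

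| rho (assumed) | Information lost | 132 × (1 + rho)/2 | N needed with T0 adjustment | Power at 132 with T0 adjustment |
|---|---|---|---|---|
| 0.5 | 25% | 99.0 | 100 | 98.6% |
| 0.6 | 20% | 105.6 | 106 | 98.1% |
| 0.7 | 15% | 112.2 | 114 | 97.4% |
| 0.8 | 10% | 118.8 | 120 | 96.7% |
| 0.9 | 5% | 125.4 | 126 | 95.9% |
| 0.95 | 2.5% | 128.7 | 130 | 95.5% |

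**4. Simulation check.** With 66 per arm and no true effect, 8,000 replicates gave adjusted-to-change variance ratios of 0.81 at rho 0.6 and 0.96 at rho 0.9, against 0.80 and 0.95 from the formula. The difference of about 0.01 is consistent with the small price of estimating the slope. Both estimators were centred near zero.

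**5. What a chance T0 imbalance does.** Given an imbalance d, the change-score estimate shifts by −(1 − rho)·d. With an assumed SD of 100 m and 66 per arm, d has SD 100 × √(2/66) = 17.4 m. The shift therefore has SD 7.0 m at rho 0.6 and 1.7 m at rho 0.9, against change-score standard errors of 15.6 m and 7.8 m. The squared ratios are 0.20 and 0.05, exactly the losses in step 3. This is the same precision loss seen from another side.

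**The case against.** The strongest reply is that the article specifies a valid, unbiased effect measure in advance, and that the gain from changing it is unknown and may be small. That stands in part. At rho 0.9 the loss is only 5%, and if 95% power at 132 is accepted, adjustment raises it only to 95.9%. It is also fair that covariates are often left to an analysis plan, which is not shown here. But the article does state the effect measure, the method and the baseline tests, and adding T0 as a covariate later would depart from what is published.

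Several stronger readings are tempting and are not supported:

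- **A fixed loss of 5–20%.** That is (1 − rho)/2 for rho between 0.9 and 0.6, and the document gives no rho.
- **T0 imbalance biases the result.** It does not, over randomisation. Subtraction already removes part of the imbalance, and step 5 shows that the rest is the variance loss already counted.
- **Power is very low.** With an assumed SD of 80 m and 66 per arm, a two-sample test of change has 46% power at rho 0.7, against 52% with adjustment; at rho 0.9 it is 89.5% against 90.9%. The low level comes from the assumed SD, not from omitting T0, and this is not the planned ANOVA.
- **Secondary outcomes are wrongly unadjusted, or EuroSCORE and surgery type wrongly unused.** Section 2.10 describes no secondary analysis. Silence in a condensed article does not show how these will be handled.
- **Baseline p-values will drive covariate choice.** Section 2.10 does not say so.

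**Conclusion.** The point holds as one about efficiency. The stated primary contrast is unbiased but less precise than a T0-adjusted comparison, by (1 − rho)/2 if the SDs at T0 and T2 are equal: 25% at rho 0.5, 15% at 0.7, 5% at 0.9, 2.5% at 0.95. Where this trial falls in that range cannot be read from the document. The result concerns the T0–T2 contrast that sections 2.5 and 2.9 call primary; section 2.10 does not say which term of the repeated-measures ANOVA tests it. The baseline significance tests serve no purpose in a randomised comparison. Validity is not in question, but the improvement needs no additional patients or measurements and is worth making before analysis.

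**What to change.** In section 2.10:

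- Define the primary estimate as the arm difference in T2 6MWD from a linear model with arm and T0 6MWD, T0 being a prespecified covariate. A mixed model over the visits with baseline means constrained equal, reporting the T2 contrast, is an equivalent route.
- Keep the 20 m target. Regressing T2 or T2 − T0 on arm and T0 gives the same arm coefficient, so the estimate still reads as a difference in change.
- Replace the baseline t and chi-square tests with a descriptive table without p-values.

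In section 2.8, make clear that the T0 walk is completed before allocation is revealed. Section 2.7 says participants cannot be masked, and a walk taken by someone who knows the assigned arm may not be a clean baseline for either adjustment or subtraction.

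Cost: T0 6MWD is already collected and SPSS and R both fit the model, so section 2.10 needs only rewording. If T0 walks are in practice done after allocation is known, the order of the baseline visit must also change, which is more than wording.

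### The T0–T2 change in 6MWD is labelled the primary analysis, but the test named and sized for it is a four-measurement repeated-measures ANOVA whose standard tests do not isolate that contrast

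*Protocol article*

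**What the plan says.** The Outcomes section (2.5) defines the primary outcome as the between-group difference in absolute change in 6MWD "between T0 and T2 (primary analysis), as well as between T0 and T3". Table 1 schedules 6MWD at T0 (baseline), T1 (admission), T2 (the day before surgery) and T3 (after surgery, before discharge).

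The Sample size section (2.9) again marks T0–T2 as the primary analysis and sets 20 m as the between-group difference worth detecting. It then bases the calculation on a "repeated-measures ANOVA with an alpha error of 5% and power of 0.95, with two groups and four measurements". The result is given as "The estimated sample size required was 132 patients", which is raised to 152 for attrition.

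The Statistical analysis section (2.10) has one sentence on the primary outcome: "To analyze differences in primary outcomes, we will use repeated-measures analysis of variance". It names no model term, no visits and no contrast.

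**The concern.** The document labels one contrast as primary and then names and sizes a test of something else. With two groups and four visits, a repeated-measures ANOVA prints two p-values that involve treatment:

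- **Group effect.** This compares group means averaged over T0, T1, T2 and T3. T0 precedes the intervention, so it can only dilute an effect.
- **Group-by-time interaction, 3 df.** This asks whether the group difference varies in any way over the four visits. A difference that appears only at T3 is enough to make it significant.

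T3 is the only visit after open-heart surgery, so a group difference confined to T3, or one that fades by T3, is plausible. A significant result from the named analysis would then not show that the programme improved walking distance before surgery, and a non-significant group effect could hide that it did. The choice between the two p-values would also be open when the data are read.

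**Working it through.** **Inputs from the document:** two groups, 1:1; four measurements; alpha 0.05; power 0.95; evaluable N = 132 (66 per arm); target 20 m in T0–T2 change; 15% attrition; 152 enrolled.

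**Inputs not in the document, assumed here:** effect size f, SD of 6MWD, and correlation rho between visits.

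**1. The plan's own N.** The G*Power formulas with f = 0.25 and rho = 0.5 give:

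- Between-groups test: lambda = f²·N·m / (1 + (m−1)·rho) = 0.0625 × 132 × 4 / 2.5 = 13.2, on 1 and 130 df. Power is 0.950 at N = 132 and 0.947 at N = 130, so 132 is reproduced.
- Interaction test: lambda = f²·N·m / (1−rho). N = 36 already suffices (lambda 18, power 0.952), so 132 is not reproduced.

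If these inputs were used, the trial was sized for the group difference averaged over all four visits.

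**2. What 132 means for the labelled contrast.** A two-sided comparison of T0–T2 change at 20 m has 95% power with 66 per arm if the SD of change is at most 20 / [(1.960 + 1.645) × √(2/66)] = 31.9 m. Total N for 95% power is 82 at an SD of change of 25 m, 118 at 30 m, 160 at 35 m, 208 at 40 m and 326 at 50 m.

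**3. The candidate tests side by side.** Take 66 per arm, SD 40 m at each visit, rho = 0.5, and group differences d at T0/T1/T2/T3 with mean d̄. The noncentralities are:

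- Group effect: 33·d̄² / [1600 × (1 + 3·0.5)/4] = 33·d̄² / 1000
- Interaction: 33·Σ(d − d̄)² / [1600 × 0.5] = 33·Σ(d − d̄)² / 800
- T0–T2 change: 33·(d at T2 − d at T0)² / [2 × 1600 × 0.5] = 33·(…)² / 1600
- ANCOVA at T2 given T0: 33·(d at T2)² / [1600 × (1 − 0.25)] = 33·(…)² / 1200

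For 0/10/20/20, d̄ = 12.5 and Σ(d − d̄)² = 275. The noncentralities are 5.16, 11.34, 8.25 and 11.0. For 0/0/0/20, d̄ = 5 and the sum is 300. The noncentralities are 0.825, 12.375, 0 and 0.

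| Differences (m) | Group effect | Interaction | T0–T2 change | ANCOVA at T2 |
|---|---|---|---|---|
| 0/10/20/20 | 0.62 | 0.81 | 0.81 | 0.91 |
| 0/10/20/0 | 0.27 | 0.81 | 0.81 | 0.91 |
| 0/0/0/20 | 0.15 | 0.85 | 0.05 | 0.05 |

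Simulation agrees: 0.84–0.86 for the interaction in the last row, and about 0.90 for ANCOVA in the first two.

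**4. Sensitivity.** At rho = 0.8 the T3-only interaction rejects in over 99% of trials. Under a non-spherical covariance (SDs 60/60/60/90 m, preoperative correlations 0.9, correlations with T3 0.4) it rejects in about 37% uncorrected and 27% with a Greenhouse-Geisser correction. There, with 0/10/20/20, the interaction has about 34% power uncorrected and 21% corrected, the group effect about 24%, and the direct T0–T2 contrast about 99%.

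**5. If patients without T3 were deleted.** Enrolling 152 with 15% loss leaves 129, or 64.6 per arm. A further 5% or 10% loss at T3 (assumed) leaves 61.4 or 58.1. Normal-approximation power for the T0–T2 change, Φ(20 / [SD·√(2/n)] − 1.96), falls from 0.811 to 0.791 or 0.769 at an SD of change of 40 m. At 31.9 m it falls from 0.946 to 0.935 or 0.923.

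**The case against.** The best defence is that repeated-measures ANOVA is not in itself the wrong method. Run on T0 and T2 alone, its group-by-time F equals the square of the change-score t, and a four-visit model can carry a planned T0–T2 contrast. Section 2.10 excludes neither, and an unseen analysis plan may supply one. This stands against any claim that the named method cannot answer the question. It does not remove the point, because the article ties the method to four measurements in 2.9, and the N stated there matches the four-visit group average under common inputs.

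Readers might infer four stronger things that the document does not support:

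- **That 85% is a false-positive rate.** Section 2.5 names T0–T3 alongside T0–T2, so a T3-only effect is an effect on part of the stated outcome. The figure shows only that the interaction does not isolate T0–T2.
- **That patients missing T3 will be dropped.** No missing-data rule is given. Deletion follows only if a classical complete-case ANOVA is run on all four visits, and the power cost in step 5 is modest.
- **That non-sphericity inflates type I error.** Under the covariance in step 4, an uncorrected interaction test rejects in about 9% of null trials, but a Greenhouse-Geisser correction brings this to about 5%. Whether one is used is analysis-plan detail.
- **That the two uses of 20 m conflict.** Section 2.5 says "a change of 20 meters from the baseline was deemed significant", while 2.9 uses 20 m between groups. No planned test uses the within-patient threshold.

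It is also fair that the interaction loses no power against the change score in the SD 40 m, rho 0.5 scenario. The step from 81% to 91% comes from baseline adjustment.

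**Conclusion.** The point holds in this form: the contrast labelled primary and the test named and sized for it do not match, and the document does not say which term or contrast decides the trial. The main objection is what the p-value means; lost power is secondary.

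The size depends on values that the document does not give. A T3-only effect of 20 m makes the interaction significant in about 85% of trials at SD 40 m and rho 0.5, and in 27–37% under the non-spherical covariance. Relying on the group effect costs most: about 62% power with effects of 0/10/20/20 m, and 27% if the benefit has gone by T3. That the trial was sized for the group effect is an inference from assumed f and rho, not a statement in the document. Loss of patients without T3 is conditional and is not part of the finding.

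**What to change.** In 2.10, name one primary test: the between-group difference in 6MWD at T2 adjusted for T0 6MWD. Estimate it by ANCOVA, or as the T2 contrast of a mixed model that uses all available visits. Report the difference with a 95% confidence interval, read against the 20 m between-group target. Make T0–T3 a secondary contrast and say so in 2.5.

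An unadjusted T0–T2 change score would also match the outcome as defined. Adjustment is preferable because, with equal SDs at both visits, its variance is (1 + rho)/2 times that of the change score: 25% lower at rho = 0.5 and 10% lower at rho = 0.8.

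Section 2.9 should then state the SD and correlation assumed for that contrast, so that the power of 132 evaluable patients can be read off.

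The cost is wording in the protocol and analysis plan. No visit or measurement changes, and the named software fits either model.

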## Discussion

3.

Although enhanced recovery has been recommended and practiced for years in cardiac surgical patients, prehabilitation before surgery has not received sufficient attention. Due to impaired cardiopulmonary function and limited daily activities, patients are at risk of functional deterioration while waiting, which could lead to surgical delay and form a vicious circle (22). Another important consideration is the waiting time and duration of prehabilitation. A study reported that a delay of more than 7 days in patients requiring CABG was associated with worse in-hospital and long-term outcomes (23). Therefore, there is a need for short-term prehabilitation programs to quickly prepare patients for surgery. Further research is required in this field to better understand the clinical effectiveness of a short-term prehabilitation programs before surgery and to combine home and hospital prehabilitation as an effective bridge to achieve preoperative readiness.

The aim of this study is to investigate the impact of the prehabilitation on preoperative readiness and postoperative recovery. To date, while studies have mainly focused on postoperative functional performance and recovery (10), there is increasing evidence that preoperative readiness is essential for successful postoperative recovery. In particular, patient readiness for surgery has been associated with shorter mechanical intubation times and reduced length of stay after CABG (24). Preoperative frailty is also an important indicator in preoperative decision-making and can help predict patient recovery trajectory (25). It is also worth noting that patients undergoing cardiac surgery often experience high levels of preoperative anxiety (26), highlighting the importance of psychological interventions to improve patients' preoperative psychological readiness. In addition, malnutrition has been linked to a longer postoperative recovery time and higher risk of cardiovascular and infectious complications (13), indicating the need for a multimodal prehabilitation that includes elements to improve physical, psychological, and nutritional factors. To address these needs, we have designed a three-arm program that incorporates exercise, nutritional optimization, and mindfulness.

This study will implement a comprehensive prehabilitation program that will be both home- and hospital-based, covering the entire waiting period before surgery. Our proposed prehabilitation program is designed to optimize preoperative and postoperative physical function performance and improve psychological well-being by enhancing physical function and alleviating psychological distress. This program was designed and will be supervised by physiotherapists, psychologists, nutritionists, cardiac rehabilitation nurse specialists, and cardiac surgical physicians, and the intensity of the program will be tailored to each patient's needs to ensure safety and effectiveness both practiced at home and in hospital. If this program is proven effective, it could provide significant benefits to patients on the waiting list by offering home-based prehabilitation and continuing care programs after hospital admission and postoperative recovery.

This study has some limitations. First, the study only includes patients awaiting for CABG and/or valve surgery. Second, this is a single-center study. Therefore, further multicenter studies including more patients with various diagnoses are needed. Third, due to the time window of 7 days, although the nutritional intervention may be beneficial for postoperative recovery, measurable changes in body composition or serum albumin concentrations may not be detectable.
